**Fig. 4 Fig4:**
[figure not shown]
Flowchart following patients from inclusion to final data collection

### Outcomes

The effects of patient-initiated follow-up (open access telePRO) will be evaluated with regard to three different aspects: resource utilisation, quality of care, and the patient perspective. Resource utilisation will constitute the primary outcome, measured by number of contacts. Quality of care and the patient perspective constitute the secondary outcomes. Quality of care includes pivotal clinical quality measures (mortality, seizure, and treatment side effects) as well as more general patient-oriented quality measures (well-being and general health). The patient perspective includes measures related to self-management, such as health literacy, self-efficacy, and patient activation. Measures of confidence, safety, and satisfaction will be used to describe patient experiences. The patient perspective is primarily explored by qualitative methods in a complementary PhD study. An overview of primary and secondary outcomes, data sources, and measurement timeline is shown in Table 1.

### Primary outcome

#### Resource utilisation

Number of contacts includes all contacts with the outpatient clinic in the study follow-up period, including face-to-face consultations with a physician, face-to-face consultations with a nurse, and telephone consultations. In addition, other health care contacts will be gathered, e.g., epilepsy-related emergency room visits and hospitalisations as well as hospitalisation related to co-morbidity. Data will be gathered from the Hospital Business Intelligence Register in Central Denmark Region.

### Secondary outcomes

#### Quality of care

Patients’ well-being will be measured by using the Danish version of WHO-Five Well-being Index (WHO-5). WHO-5 was developed by the World Health Organisation for the assessment of well-being among patients with diabetes [20]. WHO-5 consists of five positively worded items reflecting present mental well-being within the previous two weeks. Items are rated on a 6-point scale ranging from 5 “all of the time” to 0 “at no time”. The instrument has demonstrated sufficient psychometric properties in a wide range of chronic conditions [20, 21]. Patients’ general health will be measured by using one item from the Danish version of The Short Form Health Survey (SF-36); *“In general, would you say your health is: excellent, very good, good, fair, or poor”* [22, 23]. The validity and reliability of this item are well documented [24]. Data on mortality will be gathered from the Hospital Business Intelligence Register in Central Denmark Region. Finally, number of seizures and treatment side effects will be collected from ad hoc items in the epilepsy questionnaire used at epilepsy clinics in Central Denmark Region. The validity and reliability of these items have not yet been documented.

### Patient perspective

Health literacy will be measured by using the Danish version of Health Literacy Questionnaire (HLQ) [25, 26]. HLQ was developed to measure a wide range of health literacy needs of people in the community. The HLQ includes nine conceptually subscales with a total of 44 items containing five scales with agree/disagree response options and four scales with difficulties in perform tasks response options. The HLQ has well-documented psychometric properties [26]. In this study, the HLQ subscales 4, 6, and 9 will be used; *4. Social support for health, 6. Ability to actively engage with healthcare providers, 9. Understand health information well enough to know what to do.* Self-efficacy will be measured by using the Danish version of General Self-Efficacy Scale (GSE) [27, 28]. GSE was designed to assess optimistic self-belief to cope with difficult demands in life [27, 28]. GSE includes ten items with a response range from 1 “not at all true” to 4 “exactly true”. The GSE scale has been used in a range of research projects in different countries and populations, where it typically yielded sufficient psychometric properties [29]. Patient activation will be measured by two ad hoc items developed with inspiration from the Danish version of the Patient Activation Measure (PAM) [30]. Confidence, safety, and satisfaction will be measured by using ad hoc items developed with inspiration from a Danish PREM (patient-reported experience measure) questionnaire from the Danish Cancer Society.

In addition, the patient perspective will be explored in a complementary qualitative PhD study. The primary aim of this study is to explore the mechanisms of actions related to standard telePRO and open access telePRO. Interpretive description (ID) will be used as the research approach [31]. Patients’ experiences with telePRO will be explored in individual interviews and participant observations in outpatient clinics. The target group for participation is patients with epilepsy, referred to standard telePRO or open access telePRO follow-up in the three neurological departments in Central Denmark Region.

### Other measurements

Demographic information such as sex, age, education, marital status, and duration of epilepsy diagnosis will be obtained from baseline questionnaires.

### Sample size

Statistical power was estimated for the primary outcome number of contacts. Based on literature review [32] the number of consultations (n) and standard deviation (SD) was; *n* = 4.64, (SD = 2.38) in conventional follow-up and *n* = 4.12, (SD = 3.41) in open access follow-up. We expect at least a difference of one contact between the groups. Given a statistical power of 90%, *p*-value 0.05, and allocation ratio 0.8, we will need a sample size of 172 patients in the standard telePRO group and 214 patients in the open access telePRO group. To account for attrition and loss to follow-up, we will recruit a total of approximately 500 participants. For qualitative data, a purposeful sample of at least five participants from each group will be interviewed.

### Analyses

Descriptive statistics will be used to describe differences in the baseline characteristics of participating patients in the two arms of the trial. Statistical analysis will be intention to treat, whereby all randomised participants will be included in the analysis according to their randomised allocation. The primary outcome, total *number of contacts* in the two arms*,* will be analysed using a sample t-test. If the distribution of data is skewed, we will use medians and nonparametric tests. For secondary outcomes, a chi-square test or logistic regression will be used for dichotomous outcome data and sample *t*-test or multiple linear regression analysis will be used for continuous outcome data. Non-parametric tests will be used if continuous data are not normally distributed. Demographics covariates (sex, age, education, marital status, and epilepsy diagnosis duration) will be included in the per- protocol analysis.

For qualitative data, ID will be employed as the overriding research approach. ID is an inductive research strategy in which constant comparative method with concurrent data collection and analysis is utilised to gain a deeper insight and understanding of human experiences within their natural context. The result is a comprehensive interpretation, potentially a *model of explanation* of the phenomenon under study, which can provide clinical practice with a research-based choice of action [31]. ID is considered appropriate in the present study because the approach is suited for exploration of specific clinical issues, in this case how patients with epilepsy experience standard and open access telePRO follow-up.

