*AmbuFlex* is a generic clinical PRO system which is not limited to specific patient groups, organisations or medical record systems [12]. As of December 2015, AmbuFlex had been implemented in nine patient groups at 15 outpatient clinics in Denmark [13]. An analysis initiated by the Danish government based on experiences with AmbuFlex has demonstrated a positive national business case and considerable quality gain [14]. The Danish government and Danish regions, who run the public hospitals, have decided on an agreement for nationwide implementation of PRO in three diagnostic group, including epilepsy, before 2020. AmbuFlex was implemented for epilepsy outpatients at Aarhus University Hospital in March 2012 and is now used at three neurological departments in the Central Denmark Region. As of August 2016, 4,513 epilepsy outpatients have been referred to AmbuFlex, which are about two-thirds of all epilepsy outpatients in the region. The PRO questionnaire used contains information on specific aspects of daily life with epilepsy and has been developed in close cooperation with clinicians and patients. Face validity is fundamental and has been ensured during the development of the questionnaire [12, 13]. A graphical PRO overview is presented to the clinicians, who use the PRO data for clinical decisions together with other available clinical data in the record to decide whether the patient needs a visit or not. If a PRO questionnaire is used to evaluate the patient’s need for a hospital visit, the PRO data must be obtained outside the hospital. This is called tele-patient-reported outcome (telePRO) [12]. Experiences from epilepsy outpatient clinics have shown that of 8,256 PRO-based contacts, 48% were handled without additional contact to the patient other than the PRO questionnaire [13]. A preliminary interview study has indicated that patients experience greater flexibility in care, the saving of time, improved communication with the clinicians, and increased knowledge about their own disease [13, 15].

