### Intervention

#### Reference group – standard telePRO

AmbuFlex (standard telePRO) is used in three epilepsy outpatient clinics in Central Denmark Region. In standard telePRO, outpatient follow-up activity is determined by a clinician and patients receive a questionnaire at fixed intervals (3, 6, or 12 months). The questionnaire includes information about aspect of daily life with epilepsy such as seizures, symptoms, medication adherence, and social aspects. Responses are automatically processed according to a specific algorithm and given a “green”, “yellow”, or “red” status. A red status indicates that the patient needs or wishes contact with the clinic, a green status that the patient has no current need of attention, while a yellow status indicates that the patient may need to be seen in the clinic, but a clinician has to decide whether further contact is needed. The patient can always overrule a decision by requesting contact. They can choose two different contact forms in the questionnaire: telephone consultation or a face-to-face consultation at the clinic. Non-responders get three reminders and are contacted if do not respond. Clinicians keep track of incoming yellow and red responses, and non-responders, and this information is presented on a PRO alert list. The PRO overview (Fig. 1) is presented graphically to the clinician within the electronic health record system, and used as decision aid together with other available health record information to decide whether the patient needs a visit or not [13].

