**Fig. 2 Fig2:**
[figure not shown]
The open access telePRO website “My Epilepsy”. Note: Labels were translated from Danish

The website consists of four core elements:Answer questionnaire: Here, patients can answer the epilepsy questionnaire when they need to get in contact with the clinic. The questionnaire is the same as in standard telePRO. When the patient has completed the questionnaire, the response is automatically sent as a red request to the PRO alert list at the epilepsy clinic. The clinician assesses the response and contacts the patient as soon as possible. The clinic has reserved appointments in their booking system to ensure that patients get a quick appointment. As a “safety net”, patients have to answer the questionnaire before twice the fixed interval has elapsed. For example, if the patient is referred with a 12-month interval, the patient has to respond within two years. If not, the patient is automatically sent a questionnaire, given a red status, and is contacted by a clinician.Previous answers: In this element, all of the patient’s previous questionnaire responses are available. Patients have access to a PRO overview interface and specific and detailed questionnaire responses in the same manner as the clinicians. The overview interface is shown in Fig. 3. It is customised to monitor selected PRO data and to illustrate changes in health status over time. Colour codes indicate the severity of the symptoms reported by the patient. A red or orange bar indicates a self-reported problem, a yellow bar some problem, and green bar indicates no problems.

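### The primary ITT comparison is unadjusted although the assigned 3/6/12-month interval, known before randomisation, is built into contact frequency: a missed gain in precision, not an error

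*Protocol article*

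**What the plan says.** The Analyses section makes the main analysis intention to treat: "all randomised participants will be included in the analysis according to their randomised allocation". For the primary outcome, the total number of contacts "will be analysed using a sample t-test". The fallback is: "If the distribution of data is skewed, we will use medians and nonparametric tests". Neither method takes a covariate. Covariates for this comparison appear once: "Demographics covariates (sex, age, education, marital status, and epilepsy diagnosis duration) will be included in the per- protocol analysis". The assigned interval is not among them.

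The interval matters in both arms. In standard telePRO, "patients receive a questionnaire at fixed intervals (3, 6, or 12 months"). In open access, the description of the website under Fig. 2 sets a safety net: "patients have to answer the questionnaire before twice the fixed interval has elapsed". If a patient does not respond in that time, a clinician makes contact. The inclusion criteria require that patients are already referred to standard telePRO, so each has an interval before randomisation.

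On the outcome source, the Resource utilisation section says: "Data will be gathered from the Hospital Business Intelligence Register in Central Denmark Region". Table 1 lists this measure for months 0–18 only.

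**The concern.** The interval fixes how often a standard-arm patient is asked for a questionnaire, and questionnaires lead to contacts. Part of the spread in contact counts is therefore predictable before randomisation. An unadjusted test leaves that part in the error term, and any chance difference between the arms in interval mix passes into the estimated effect. None of the covariates that the plan does name is tied to the contact schedule in this way.

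Precision matters here because the Discussion says the two follow-up forms are rather similar and will probably differ only slightly. In addition, the ITT and per-protocol results will differ in adjustment as well as in population. If they disagree, the reason will be harder to read.

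**Working it through.** **1. The plan's own sample size.** Inputs from the Sample size section: SD 2.38 (conventional) and 3.41 (open access), difference 1, power 90%, p-value 0.05 (taken as two-sided), ratio 0.8. The formula for two means with unequal SDs is n₁ = (1.960 + 1.282)² × (SD₁² + SD₂²/k) / 1², with the squared sum equal to 10.507.
- k = 0.8: 10.507 × (5.664 + 11.628/0.8) = 212.2, so 213, and 0.8 × 212.2 = 169.8, so 170. The stated figures are 214 and 172. They reproduce within two patients, with the larger number on the arm with SD 2.38, that is, with the arm labels exchanged.
- Welch power is 90.1% with the labels exchanged and 92.2% as labelled (172 standard, 214 open access).

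The calculation contains no adjustment, so the trial is sized for the unadjusted test.

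**2. Gradient by interval in the standard arm.** Scheduled questionnaires in 18 months: 18/3 = 6, 18/6 = 3, 18/12 = 1.5 (an average rate). The Background reports that of earlier PRO-based contacts "48% were handled without additional contact to the patient other than the PRO questionnaire", so 52% led to something further. If that share applies at every interval (an assumption), expected contacts are 0.52 × (6, 3, 1.5) = 3.12, 1.56 and 0.78, a fourfold gradient.

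**3. Share of variance explained.** The interval mix is not given, so mixes are assumed. The between-interval variance is v = Σp(x − mean)². The average planning variance is (5.664 + 11.628)/2 = 8.646. The Poisson column is v/(v + mean).

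| Mix 3/6/12 months | Mean | v | v / 8.646 | Poisson |
|---|---|---|---|---|
| 5/15/80% | 1.01 | 0.310 | 3.6% | 23% |
| 10/30/60% | 1.25 | 0.511 | 5.9% | 29% |
| 20/40/40% | 1.56 | 0.730 | 8.4% | 32% |
| equal thirds | 1.82 | 0.946 | 10.9% | 34% |

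With negative binomial counts (within-interval variance = mean + dispersion × mean², dispersion 0.3–1.0) and mixes 5/25/70, 10/30/60 and 20/30/50%, R² is 11–25%. These models have total SDs of about 1.4–2.3, below the planning SDs.

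**4. What this buys.** The standard error falls by 1 − √(1 − R²): 2.0% at R² = 0.04, 5.7% at 0.11 and 18.8% at 0.34. The table uses 172/214 and the plan's SDs.

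| R² | Power, difference 1 | Power, difference 0.52 |
|---|---|---|
| 0 | 92.2% | 41.9% |
| 0.10 | 94.5% | 45.7% |
| 0.30 | 98.1% | 55.5% |

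The 0.52 is the difference between the two means cited in the Sample size section, 4.64 − 4.12.

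**5. If the gradient is weaker under open access.** The safety net falls at 6, 12 or 24 months, and the last lies outside the 18-month window. Take the extreme of no gradient in that arm, with about 500 patients split 225/275 and mix 10/30/60%. The variance of the difference is 5.664/225 + 11.628/275 = 0.0675. The common interval slope becomes 0.45 of the standard-arm gradient. The standard-arm term falls by 0.511 × (1 − 0.55²)/225 = 0.00158 and the open access term rises by 0.511 × 0.45²/275 = 0.00038. The net saving is 0.0012/0.0675 = 1.8%, against 0.511 × (1/225 + 1/275)/0.0675 = 6.1% with the full gradient in both arms.

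**6. Chance imbalance, if allocation is not stratified by interval.** One standard error in the between-arm difference in the 3-month share is √[p(1 − p)(1/225 + 1/275)] = 2.0, 2.7 and 3.6 points for p = 5%, 10% and 20%. If 3-month patients replace 12-month patients, the difference moves by that share × (3.12 − 0.78) = 0.05, 0.06 and 0.08 contacts. The standard error of the difference is √0.0675 = 0.26, so the shift is a third of one standard error or less.

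**The case against.** Under randomisation the unadjusted comparison is valid: its type I error already allows for chance imbalance, and the sample size assumes no adjustment. A reader might infer that the primary test is biased or the trial underpowered on this ground. The documents support neither.

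A reader might also infer that interval and previous contacts are the strongest predictors of the outcome. The article reports no association for either. For interval the link is an inference from the design. For previous contacts it is an assumption, and a pre-randomisation extract is not a listed measurement.

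A gain worth 12–33% more patients, which is 1/(1 − R²) − 1 at R² = 0.11–0.25, is tempting to quote. It needs counts less variable than the plan's SDs. Those SDs come from another study of conventional and open access follow-up, so neither basis is certain. The gradient is also derived for the standard arm only.

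Adjusting a per-protocol analysis but not the ITT analysis is defensible, because only the latter keeps the protection of randomisation. All of this stands. It limits the size of the point but leaves the case for using a known, design-linked covariate. Nor is this a detail left to an unseen analysis plan, since the article names the primary test and says where covariates enter.

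**Conclusion.** The point holds as a missed efficiency gain. The primary ITT analysis uses no baseline information, although the interval is known for every patient and tied to contact frequency in both arms.

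The gain is small to material. Interval explains about 4–11% of variance on the plan's own SDs (standard error down 2–6%) and roughly 11–34% if counts vary less than planned. These ranges rest on assumed interval mixes, on the 52% share applying at every interval, and on a similar gradient in both arms. With no gradient under open access, the saving in variance at a 10/30/60% mix is about 2%. At a true difference of one contact the trial does not need the gain. At the small differences that the Discussion expects, it does help, though adjustment for interval alone would not make a difference of 0.52 well powered.

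**What to change.** Prespecify the primary ITT analysis as a linear model for number of contacts with arm and assigned interval (categorical), with robust standard errors. The effect then remains a difference in mean contacts, the quantity used in the sample size calculation. Keep the unadjusted t-test as a sensitivity analysis, and state where the skewness fallback then stands. Add interval to the per-protocol covariates. If contacts before randomisation can be extracted from the same register, include them as a further covariate.

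The cost is a line or so of analysis wording and at most one extra register field. Patients are not asked for anything new, and the sample size need not change.

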### Objectives

The aim of this study is to provide insight into the effects of patient-initiated telePRO follow-up. The specific aims are to compare resource utilisation, quality of care, and the patient perspective of two outpatient follow-up activities: a) standard telePRO (fixed-interval telePRO follow-up) and b) open access telePRO (patient-initiated telePRO follow-up). We hypothesise that 1. Number of contacts is less in open access telePRO, 2. Quality of care in open access telePRO is at least as good as in standard telePRO, and 3. Patient self-management and experiences in open access telePRO are better than standard telePRO.

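### The skewness rule would replace the comparison of mean contacts with a rank comparison, which can show fewer contacts in open access when mean contacts are equal

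*Protocol article*

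**What the plan says.** Everything except the fallback in the protocol article points to a comparison of means.

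- **Objectives:** the first hypothesis is "Number of contacts is less in open access telePRO".
- **Outcomes and Primary outcome:** number of contacts is the measure of resource utilisation, counted from a hospital register over the follow-up period.
- **Sample size:** planning values come from a cited study, with mean 4.64 ("SD = 2.38) in conventional follow-up") and mean 4.12 ("SD = 3.41) in open access follow-up"). The target is a difference in means: "We expect at least a difference of one contact between the groups". Power is 90%, with "value 0.05, and allocation ratio 0.8". This gives 172 standard and 214 open access patients, with about 500 to be recruited.
- **Analyses:** the total number of contacts, by randomised allocation, "will be analysed using a sample t-test". The next sentence is the fallback: "If the distribution of data is skewed, we will use medians and nonparametric tests". No criterion for skewness is given and no nonparametric test is named.

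**The concern.** Clinic workload is the mean number of contacts per patient times the number of patients. A difference in means therefore bears directly on the resource question. A difference in medians or in ranks does not. A rank test asks whether a randomly chosen open access patient tends to have fewer contacts than a randomly chosen standard patient. If one arm has both more low users and more high users, that answer can be yes while the clinic handles the same number of contacts.

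The rule thus lets the shape of the observed data decide which of two questions the primary analysis answers. The fallback is also the likelier branch: with mean 4.12 and SD 3.41, zero lies only 4.12/3.41 = 1.2 SDs below the open access mean, so a roughly symmetric distribution is hard to achieve. At stake is a primary conclusion that open access reduces contacts when the total is unchanged.

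**Working it through.** **1. The plan's sample size is a comparison of means.** Use the unequal-variance normal formula, two-sided 5% (sidedness is not stated, so this is assumed), 90% power, δ = 1: n₁ = (SD₁² + SD₂²/k)(1.960 + 1.282)²/δ², with n₂ = k·n₁ and (1.960 + 1.282)² ≈ 10.507.

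- SD₁ = 2.38, SD₂ = 3.41, k = 0.8: (5.664 + 11.628/0.8) × 10.507 = 212.2, so 213 and 170. A Welch t version gives about 214 and 171. This matches the stated 214 and 172, but it places SD 2.38 on the larger arm, opposite to the labels.
- SDs on the arms as labelled, k = 1.25: (5.664 + 11.628/1.25) × 10.507 = 157.3, so 158 and 197. The stated 172/214 then has about 92% power, so the swap costs nothing.

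**2. Simulation set-up.** Both arms have the same true mean (4.64, 4.38 or 4.12: the two planning means and their midpoint), with SD 2.38 in standard and 3.41 in open access. Sizes are 172/214 (stated requirement) and 225/275 (500 × 0.45 and 500 × 0.55). Two inputs are assumptions, not in the document: the counts are negative binomial with size k = μ²/(SD² − μ), and the nonparametric test is Mann-Whitney at two-sided 5%. There were 3,000–10,000 trials per setting.

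**3. Mechanism at μ = 4.38.** k = 19.18/(5.66 − 4.38) = 14.9 for standard and 19.18/(11.63 − 4.38) = 2.65 for open access. Under these distributions about 23% of standard and 34% of open access patients have two contacts or fewer, and about 3% and 8% have ten or more. Means are equal but ranks favour open access.

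**4. Results, equal true means.** Percentage of trials with significantly fewer contacts in open access (nominal 2.5%):

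| Setting | Mann-Whitney |
|---|---|
| 225/275, planning SDs | 26–34% |
| 172/214, planning SDs | 21–28% |
| 225/275, 20–40% of open access decline and follow the control distribution | about 14–21% (12–25% across the three means and repeat runs) |
| 225/275, open access SD 2.9 | about 11% |
| 225/275, open access SD 2.6 | about 5% |
| 225/275, equal SDs | about 2.5% |

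With the planning SDs, significance in the opposite direction was about 0.1% or less. The Welch t-test rejected in about 5% of trials, two-sided, throughout. A skewness test at 5% fired in essentially every negative binomial trial, so a rule gated on it gave the same figures as Mann-Whitney alone.

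**5. Sensitivity to shape, planning SDs.** Gamma: 27–36% at 172/214 and 34–45% at 225/275. Lognormal: 36–43% and 41–52%. Symmetric normal: about 2.5%, but then the switch would not be used.

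**The case against.** The strongest case against has four parts.

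*The figures are conditional.* The Sample size section gives means and SDs but no distribution, and the Analyses section names no rank test. A reader might infer that the plan has a false positive rate near 30%. The document does not support that as a fact about this trial, because it rests on the negative binomial shape, Mann-Whitney, and the SDs and numbers used. Nor does a larger SD by itself show more low users with a heavier tail; that shape comes from the assumed model.

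*The SDs may not carry over.* They come from a comparison of open access with conventional follow-up, whereas this control arm is standard telePRO, and the Discussion expects the two arms to be similar. Under Randomisation, open access patients who decline stay on standard telePRO yet are analysed as allocated, which pulls the arms together. This stands, and it is why the range starts near 5%. It does not remove the problem: these are the only variance figures the plan has, and at lower means of about 1.5–2, modest SD differences still gave 11–27%.

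*The rank test is not invalid.* A reader might infer that it is. When the distributions differ, its own null is false and rejecting it is no error. The Objectives also do not say that fewer means a lower mean. This stands as well. The fault is a mismatch of question with the resource outcome and the power calculation.

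*A separate analysis plan could settle the detail.* It could define skewness and name the test. But the switch is a stated rule, so such a plan would have to reverse it, not merely complete it.

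**Conclusion.** The point holds. As written, observed skewness would replace the comparison of mean contacts, on which the trial is powered and on which resource use depends, with a comparison of medians or ranks. Skewness is very likely for these counts, although without a stated trigger its use remains an inference.

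The consequence depends on how far the arms differ in spread. Under negative binomial counts with equal means, it runs from no inflation with equal SDs, through about 5–11% at an open access SD of 2.6–2.9, to 26–34% with the planning SDs and all 500 patients analysed. When there is inflation, it favours the trial's hypothesis. The switch also protects nothing here, since the Welch test kept its error rate at these sample sizes despite the skewness.

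**What to change.** In Analyses, delete the skewness switch for the primary outcome. State instead that the primary analysis is the difference between arms in mean number of contacts, by randomised allocation, with an unequal-variance (Welch) or bootstrap confidence interval, whatever the distribution. Name one of the two in advance. Report medians and rank tests as descriptive or sensitivity analyses that do not decide the primary hypothesis. A ratio of means from a count model with robust standard errors would be an acceptable alternative but is not required.

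The cost is one paragraph of wording, with no new data, no change to the sample size and standard software. The change should be dated before contacts are compared by arm.
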